### Data collection and management

All data, including the primary outcome, will be obtained from medical records, hospital incident reporting systems, or via hospital costing units. Study data will be collected and managed using REDCap (Research Electronic Data Capture) electronic data capture tools hosted at Monash University and managed by Helix [42, 43]. EDCap is a secure, web-based application designed to support data capture for research studies, providing (1) an intuitive interface for validated data entry; (2) audit trails for tracking data manipulation and export procedures; (3) automated export procedures for seam- less data downloads to common statistical packages; and (4) procedures for importing data from external sources. On each ward, a designated allied health assistant, employed by the health service will enter data from participants’ medical record into a custom-built REDCap database. The site coordinator will review the accuracy of the study data from a random selection of 20% of participants each week. The site coordinator will randomly sample based on the availability of the medical records at the time of data review.

Every six weeks, each site’s coordinator will extract data recorded about falls from the hospital reporting system. Falls data will be reviewed by the Independent Data Safety and Monitoring Committee (DSMC) [44]. The DSMC will comprise of two experienced independent researchers who have no vested interest in the outcome of the trial and they will remain blind to ward allocation. We have prespecified a falls event rate *>* 10% over the normal upper limit, based on 12 months of historical falls data from the participating wards, as requiring intervention by the trial steering committee. Any harm suffered from participation in the trial will be managed by the health service who provided rehabilitation care.

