To differentiate My Therapy from general therapist advice and education regarding self-practice during inpatient rehabilitation and goal setting with the patient, My Therapy must also adhere to the following criteria (a) a written program, (b) therapist documentation of the program within the medical record, (c) include a feedback mechanism to the therapist (e.g., a paper based or smart device tick sheet), and (d) be actively monitored and progressed as clinically required. My Therapy is tailored to individual needs, recommended by the patient’s treating occupational therapist and physiotherapist after goal setting with the patient, and can be practiced within business hours, in the evenings or over the weekend.

A recent pilot study showed the implementation of My Therapy to be feasible in hospitalised older people with musculoskeletal conditions and frailty (n = 116) [24]. The pilot study led to around 100 min of extra weekly practice alongside usual care rehabilitation and the benefits occurred without additional staff or adverse events [24]. Compared to usual care, more than double the proportion of patients allocated to My Therapy achieved a minimal clinically important difference (MCID) in functional independence from admission to discharge [24], and it was also delivered safely in those with cognitive impairment.

The current protocol builds on this initial pilot study [24]. The project will scale-up implementation of My Therapy across inpatient and home-based rehabilitation wards in Australian public and private health networks, and evaluate the benefits and cost-effectiveness of My Therapy via a stepped-wedge cluster randomised trial design. This trial aims to determine the effectiveness of My Therapy on clinical outcomes of function and health-related quality of life, when implemented across four health networks. It will also determine the cost-effectiveness per MCID in functional independence achieved and per quality adjusted life year (QALY) gained compared to usual care; in addition to the cost of implementation. We hypothesise that My Therapy will result in improved functional independence and health-related quality of life during rehabilitation without adverse events (falls); and will be cost-effective to the health service due to a reduction in rehabilitation length of stay, compared to usual care alone.

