### Outcomes

#### Clinical evaluation

The primary clinical outcome is *functional independence*, which will be assessed using the Functional Independence Measure (FIM™) [37, 38]. The change in FIM™ from admission to discharge will be reported as the pro-portion of patients who achieve a MCID in FIM™ (22 points) [37]. The FIM™ is routinely recorded on admission and discharge from rehabilitation by accredited assessors, and will be used to report an overall score and sub-categories of motor and cognitive function.

Secondary outcomes include change in *health-related quality of life*, assessed using the EQ-5D-5L [39]; *rehabilitation length of stay*, reported as the number of overnight stays between the rehabilitation admission and discharge dates; *days at home up to 30 days after surgery (DAH30)* for any surgical patients [40, 41]; hospital re-admissions to the same health service one month (30 days) post-discharge (yes/no); discharge accommodation, categorised as home, transitional care, residential care, hospital, or death (no accommodation); need for post-discharge rehabilitation services (yes/no); and adverse events (falls), assessed as the number of falls and the number of serious falls during the rehabilitation admission, and these will be classified as occurring during or not during My Therapy participation.

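### The safety committee is kept blind to ward allocation and is given only a historical falls limit, so it cannot attribute an excess of falls to My Therapy, and a moderate or early excess can stay below the limit

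*Protocol article*

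**What the plan says.** The arrangement is set out in the protocol article under Data collection and management:

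- **Data:** "Every six weeks, each site’s coordinator will extract data recorded about falls from the hospital reporting system".
- **Reviewers:** a committee of two experienced independent researchers with no stake in the result. On masking, the text says that "they will remain blind to ward allocation".
- **Criterion:** a falls event rate more than "10% over the normal upper limit, based on 12 months of historical falls data from the participating wards". Neither the historical rate nor the limit is printed, and the text does not say whether the limit is read per ward or over all wards.
- **Consequence:** crossing the limit is prespecified "as requiring intervention by the trial steering committee". The opening of Methods/design describes that committee as investigators, site clinicians and a consumer representative. It is not stated to be blind.

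The section describes no interim comparison of falls between control and experimental conditions, masked or open, and no way for the committee to unblind. Under Clinical evaluation, falls and serious falls are secondary outcomes, to be "classified as occurring during or not during My Therapy participation". Under Statistical analyses, the remaining secondary outcomes, falls among them, are compared between groups at the end by univariable methods.

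**The concern.** Falls are the only adverse event the article names, and their absence is part of the hypothesis at the end of the Background. The intervention adds unsupervised practice, and the trial admits patients of any rehabilitation diagnosis, including those with cognitive impairment. Falls monitoring should therefore be able to answer one question: are falls more frequent on wards delivering My Therapy than they would otherwise be?

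The stated rule does not let the independent body ask it. A committee that does not know which wards are exposed, and compares only with the past, sees a rise but not where it sits in relation to the intervention.

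History is also an imperfect comparator here. The Limitations section says the two home-based wards were not initially planned, and the sample size section expects bed closures over Christmas. Changes of this kind could look like harm or hide it. The design supplies a better comparator, concurrent control wards, and the monitoring rule does not use it.

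**Working it through.** **The plan's own figure.** The trigger cannot be reproduced, because the article gives neither the historical rate nor the upper limit. What can be checked is how it behaves under stated assumptions.

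**Inputs from the article.** Eight wards and nine six-week blocks, with wards crossing over sequentially at six-week intervals (Design; Setting and participants). I read this as one ward per step, so *b* − 1 wards are exposed in block *b*, and exposed and control wards coexist in blocks 2 to 8. The average is 25 beds per ward (Sample size calculation), so a full ward-block is 25 × 42 = 1,050 bed-days.

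**Assumptions.** Equal ward sizes, Poisson counts, falls rates as given below, and *u*, the relative gap between the historical mean and its upper limit.

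**1. Limit applied to all wards pooled.** With *k* of 8 wards exposed and rate ratio RR on those wards, the pooled rate relative to history is 1 + (RR − 1) × *k*/8. The trigger is 1.10 × (1 + *u*). The RR at which the expected rate just reaches the trigger is

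RR = 1 + [1.10(1 + *u*) − 1] × 8/*k*.

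For *u* = 0 and *k* = 1 this is 1 + 0.10 × 8 = 1.80. For *k* = 2 it is 1.40, and for *k* = 4 it is 1.20.

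| Limit above mean (*u*) | 1 ward exposed | 2 wards | 4 wards | 8 wards |
|---|---|---|---|---|
| 0 | 1.80 | 1.40 | 1.20 | 1.10 |
| 0.2 | 3.56 | 2.28 | 1.64 | 1.32 |
| 0.5 | 6.20 | 3.60 | 2.30 | 1.65 |

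An upper limit would normally lie above the mean, so the first row is the most favourable to the plan.

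**2. Chance that one block crosses the pooled limit.** Take *u* = 0.2, 4 to 8 falls per 1,000 bed-days, and 5,880 to 8,400 bed-days per block (8 × 1,050, with or without a 30% reduction). With a true RR of 1.5, a block crosses with probability about 7–16% when 2 wards are exposed, 31–35% with 4, 55–65% with 6 and 73–89% with all 8. With RR = 2.0 it is about 31–35% with 2 wards and 73–89% with 4.

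**3. Limit applied per ward.** There is no dilution, but counts are small and the answer depends on the assumed limit.

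- *u* = 0.2, rates as in step 2: an exposed ward with RR = 1.5 crosses in about 60–65% of blocks, but an unaffected ward crosses in 14–34%.
- Limit at mean + 1.96 SD, 3 to 10 falls per 1,000 bed-days: an exposed ward crosses in 11–24% of blocks and an unaffected one in about 1–2%.

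Under the second limit, by the end of block 5 there are 1 + 2 + 3 + 4 = 10 exposed ward-blocks. The chance that at least one has crossed is 1 − (1 − 0.106)^10 = 67% at the low end and 1 − (1 − 0.237)^10 = 93% at the high end. An alarm somewhere is therefore likely. What is missing is the information on whether it came from an exposed ward.

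**4. Comparison by condition.** In blocks 2 to 5 there are 7 + 6 + 5 + 4 = 22 concurrent control ward-blocks against the 10 exposed. A Wald test of the log rate ratio, with SE = √(1/exposed falls + 1/control falls) and one-sided 0.025, has about 58–98% power for RR = 1.5 at 3 to 10 falls per 1,000 bed-days. This ignores differences between wards and so is optimistic. With an assumed between-ward coefficient of variation of 0.3, the same crude test gives a false-positive rate of 7–14% instead of 2.5%.

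**The case against.** The strongest reply is that the limit needs no knowledge of allocation to work. An excess that is large, or that arises once most wards have crossed over, trips it whatever its cause. The matter then passes to a steering committee that is not stated to be blind and includes site clinicians. A blind signal check followed by an informed response is a coherent arrangement. This stands, and it rules out the tempting reading that the committee cannot see an excess at all.

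It does not fully answer the point. Attribution is left to a body that includes the investigators, while the independent body lacks the means, and an excess that stays under the limit never reaches the second stage. The final between-group analysis comes too late for monitoring.

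Other inferences a reader might draw are also unsupported:

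- *The blinding protects nothing.* Staff and patients are unblinded, but masking reviewers can still limit expectation bias.
- *The during/not-during classification reveals allocation anyway.* The article defines it as an outcome and does not say that it reaches the committee.
- *This is the only safety monitoring.* Exercises are given only where judged safe, programs are actively monitored, and falls enter hospital incident systems. It is the only committee-level falls monitoring described.
- *The committee is barred from any grouped data.* Blindness to ward allocation does not exclude tables by masked group, though none is described.

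Finally, report layouts and unblinding routes often sit in a charter that is not shown. Their absence alone would be no finding. The point rests on the blinding rule and the single historical criterion, both of which the article states.

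**Conclusion.** The concern holds in a limited form. As written, the committee cannot attribute an excess of falls to My Therapy or separate it from changes over time or in case mix, and a moderate or early excess can remain below the limit.

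The size depends on assumptions the article does not settle. With pooled reading and the limit at the historical mean, the rise needed on exposed wards is 80%, 40% or 20% with 1, 2 or 4 wards crossed over, and more if the limit lies above the mean. With per-ward reading there is no dilution, but chance crossings and true ones look alike to a blind committee.

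It would be wrong to set the 11–24% chance for a single ward-block against the 58–98% power of a cumulative comparison and call the difference the loss: one is a single look at one ward, the other pools ten exposed ward-blocks. The case for change is attribution, together with early dilution if the limit is pooled. This is a cheap improvement, not a fatal flaw.

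**What to change.** Replace the blinding rule. At each six-weekly review, give the committee a closed report containing:

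- falls and serious falls per bed-day, by ward and by condition, at least as masked groups with a stated route to unblind;
- exposed wards set against concurrent control wards, and against each ward's own earlier control period.

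State also whether the existing trigger is read per ward or pooled. The trigger level remains for the sponsor to set.

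**Cost:** falls are already extracted every six weeks, so the work is one reformatted table with bed-days as denominator. There are two downsides. The committee, though not the investigators, sees comparative falls data during the trial. And with few exposed wards, crude tables by condition can reflect ward mix, for example home-based against inpatient wards, so they should be read alongside the ward-level figures and not as a stand-alone test.

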### Data Analysis

#### Sample size calculation

The sample size calculation is based on the proportional change in primary outcome measure (the FIM™) in the published My Therapy pilot study, which found that double the proportion of patients in the My Therapy group (22%) achieved a MCID in function (FIM) from admission to discharge, compared to usual care (10%) [24]. The sample size is based on a two-tailed alpha of 0.05, power of 0.99, as well as an intraclass correlation coefficient (ICC) of 0.005 (established from a previous rehabilitation study [20]). Using these parameters, the total sample size required is 2,160 patients. With an average of 25 beds per ward, length of stay of 18.5 days [45] and a data collection period of 54 weeks, each rehabilitation ward will contribute around 485 patients. Allowance has been made for this to be reduced to 340 when an opt-out rate of 30% is assumed. If each of the eight rehabilitation wards contributes 340 patients across the 54 weeks of data collection, the total of 2,716 will exceed the sample size requirement for the primary outcome measure of the proportion of people who achieve a MCID in FIM™. The sample size calculation allows for additional planned bed closures over the Christmas period and censoring of patients already admitted to the ward at the point of transition from the control to the experimental period, as these patients will be exposed to both conditions and will be censored to avoid data contamination.

#### Statistical analyses

Analyses will only include data from patients who were admitted and discharged during the ward’s control condition period or experimental condition period. Patients still admitted to the rehabilitation wards at the end point of the study will not be included. It is expected that due to the step-wedged design, this will equally exclude long-stayers in the control and experimental condition periods. Each analysis will use individual patient-level data, clustered within the ward, and will use the length of time (in weeks) of experimental exposure as an effect modifier [32]. Length of time of exposure to the experimental condition is an important consideration when an intervention may take time to settle into usual practice and where there may be a cumulative effect [32]. Analyses will be conducted on an intention-to-treat basis.

The analyses will compare the FIM™ and the health-related quality of life utility index score between the control and the intervention groups. Health-related quality of life scores from the EQ-5D-5L will be converted from raw scores to a utility index based on an Australian population [46, 47]. The proportion of people who achieve a MCID of 22 points in FIM™ [35, 37] will be analysed using mixed effects logistic regression, and the change in FIM™ score and utility index will be ana-lysed using mixed effects linear regression. Length of stay will also be analysed via a linear regression model.

While not powered for a secondary analysis, there will be an exploratory secondary analysis of the same outcome measures within each of the clusters and for the two home-based bed-substitution wards. Other secondary outcomes will be compared between groups using univariable analyses. All outcomes will be reported with 95% confidence intervals and analyses will assume a significance of *p* < 0.05.

For the economic evaluation, the primary outcome will be presented as cost-effectiveness and cost-utility analyses, reporting (i) the cost per MCID in FIM™ achieved; and (ii) the cost per QALY gained. Costs will include the rehabilitation length of stay, acute transfers within the rehabilitation stay and unplanned re-admissions within the 30 days post discharge. The QALYs will be calculated using the utility index scores.

The mean cost difference will be determined between the two groups using a linear regression model [48]. Incremental cost-effectiveness ratios will be determined for both the FIM™ and utility index using the cost as the numerator, and the utility or effectiveness data as the denominator. All analyses will use individual patient-level data, will be clustered within the ward, and will use the length of time (in weeks) of experimental exposure as an effect modifier [32]. The ICERs for the cost per MCID achieved will be analysed using mixed effects logistic regression, and the ICERs for the cost per QALY gained will be analysed using mixed effects linear regression. Confidence intervals around the individual ICERs for utility and effectiveness will be calculated using the bootstrap method with 5,000 repetitions [49]. Individual ICERs will use the central limit theorem to generate the confidence ellipses, and the cost effectiveness acceptability curves (CEACs) [49] to inform the probability that My Therapy is less costly and more beneficial compared with usual care alone, with a $50,000 per QALY gained [50] threshold to determine cost-effectiveness.

A cost-analysis will be utilised to determine the cost of implementation. Data will be presented within two time periods; (i) the preparation period while under usual care conditions as well as the three months prior to commencing My Therapy (e.g., materials purchased and staff education sessions), and (ii) the implementation period while under experimental conditions (from commencement of My Therapy through to the end of the inpatient data collection indicating business as usual). Periods (i) and (ii) together will represent the full cost of My Therapy implementation (i.e., preparation, implementation and transition to business-as-usual conditions), whereas just period (ii) will represent the costs under business-as-usual conditions (i.e., just implementation and transition to business-as-usual conditions).

As each ward will have a different time length for the preparation period and the implementation period, depending on their point of randomisation, costs will be presented per patient (total costs divided by the total number of patients who participate in My Therapy), and per ward (total costs divided by the total number of wards; n = 8) using independent *t*-tests (mean, standard deviation). Resource utilisation will be reported as real and in-kinds costs and these will include exercise materials purchased specifically for My Therapy (reported as market rate at the time of purchase); education for staff and patients, site coordinator time, marketing and communication, as well as therapist time to prescribe and progress My Therapy (staff costs based on EBA rates for Health Professionals) [51]. Costs will not include incidental nursing, medical or other staff time spent encouraging patient participation in My Therapy.

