### Design

A stepped-wedge cluster randomised trial design will be conducted over 54 weeks, involving nine blocks of six-weeks duration (Fig. 1) [32]. Randomisation refers to the time when each ward crosses over from usual care to experimental conditions. Three months prior to trial commencement, a blinded researcher, not involved in the assessment or delivery of intervention, will randomise wards to the order of commencement of My Therapy using a computer-generated number sequence. Each ward will transition from the usual care condition (control group receiving usual care) to the experimental condition (intervention group receiving My Therapy in addition to usual care) sequentially at six-week intervals until all sites have crossed over to the experimental condition. Therapists and assessors will not be blind to group allocation and they will be informed of their upcoming cross over six weeks prior to cross over. This is due to the practical need to provide My Therapy education to the staff in the six weeks prior to commencing. In addition, patients will not be blind to group allocation due to the need to educate and engage patients in the My Therapy program.

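### The stated models carry weeks of exposure but no calendar time, so part of any secular trend over the 54 weeks would be credited to My Therapy, or would mask its benefit

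*Protocol article*

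**What the plan says.** The Design section describes a stepped-wedge trial "conducted over 54 weeks, involving nine blocks of six-weeks duration", with wards crossing in random order at six-week intervals until all deliver My Therapy. Setting and participants gives eight wards.

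The Statistical analyses section sets the model structure once for all clinical analyses: patient-level data, "clustered within the ward, and will use the length of time (in weeks) of experimental exposure as an effect modifier". The reason given for the exposure term is that the intervention may take time to bed in and may have a cumulative effect. The primary outcome, achieving the FIM MCID, is analysed by mixed-effects logistic regression. Change in FIM and utility is analysed by mixed-effects linear regression, and length of stay by linear regression. The remaining secondary outcomes get univariable comparisons.

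The economic paragraphs of the same section repeat the structure: "All analyses will use individual patient-level data, will be clustered within the ward, and will use the length of time (in weeks) of experimental exposure". Here too, exposure serves as the modifier.

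Calendar time, period, step and season are not named as a model term anywhere in the article.

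**The concern.** In a stepped-wedge trial every ward moves in one direction, from control to intervention, so condition and calendar time are correlated by design. Randomising the crossover order protects the comparison fully only if the model compares wards within the same period, and that requires a calendar-time term.

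The article does choose a time variable, but a different one. Weeks of exposure are zero for all control patients, so this term carries no information on how outcomes move under usual care. After crossover it rises week for week with calendar time within a ward, so a trend can also appear as a growing effect of My Therapy. At stake are the primary test, the linear-model outcomes and both cost-effectiveness ratios.

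**Working it through.** **Inputs from the article.** Eight wards and nine six-week blocks; "The sample size is based on a two-tailed alpha of 0.05, power of 0.99"; 22% versus 10%; "intraclass correlation coefficient (ICC) of 0.005"; "the total sample size required is 2,160 patients". Since 8 × 9 × 30 = 2,160, the target equals 30 patients per ward-block.

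**Assumptions.** One ward crosses per step. Blocks are of equal size. The trend is linear, and its size is assumed because the documents give none.

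**The plan's own figure.** An unclustered two-sided calculation gives 338 per arm, 676 in total. Inflating by 1 + (m − 1) × 0.005 gives 1,585 for m = 270 and 2,312 for m = 485. The Hussey-Hughes stepped-wedge variance needs about 1,490 for 99% power. None of these two-sided calculations returns 2,160, and the article does not state its method. The target is larger than the stepped-wedge formula needs, and this does not affect the present point.

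**Timing.** There are 36 control and 36 My Therapy ward-blocks, with mean block numbers 3.33 and 6.67. The gap is 3.33 × 6 = 20 weeks. A ward crossing after block k has mean control block (k + 1)/2 and mean My Therapy block (k + 10)/2, so the gap is 4.5 blocks, or 27 weeks, in every ward.

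**Share of a linear trend entering the effect (random ward, no period term).** Let σ² be the within-ward variance of a block mean, τ² the ward variance, and ρ = τ²/(σ² + 9τ²). Generalised least squares on this layout gives:

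- share of the 54-week trend = (60/9)/(18 − 42ρ)
- variance of the effect = σ²/(18 − 42ρ)

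With ICC 0.005 and m = 30, ρ = 0.005/(0.995/30 + 9 × 0.005) = 0.0640. The share is 6.667/15.31 = 0.435, about 44%. Ignoring wards (ρ = 0) gives 0.37; ward fixed effects (ρ = 1/9) give 0.50.

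**Type I error for a 5-point drift and no true effect.** The false average effect is 5 × 0.435 = 2.2 points. The SE depends on the outcome variance:

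- 0.16 × 0.84 = 0.1344 (midpoint of 10% and 22%): SE = √(0.1344 × 0.995/30/15.31) = 0.0171
- 0.10 × 0.90 = 0.09 (usual-care rate): SE = √(0.09 × 0.995/30/15.31) = 0.0140

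The error rate is P(|N(bias/SE, 1)| > 1.96).

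| Quantity tested | False effect (points) | Type I, variance 0.1344 | Type I, variance 0.09 |
|---|---|---|---|
| Average effect, no exposure term | 2.2 | 25% | 34% |
| Effect at mean exposure (17 weeks), exposure term in | 2.3 | 27% | 37% |
| Week-0 coefficient, exposure term in, uncentred | 1.2 | 8% | 10% |

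With variance 0.1344, drifts of 3 and 8 points give false average effects of 1.3 and 3.5 points and type I errors of 12% and 53%. The week-0 coefficient gives 6% and 14%.

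**Simulation check.** Logistic model, 1,000 null trials per scenario, usual-care rate starting at 10%:

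| Rise over 54 weeks (points) | No time term | Joint test, treatment + exposure | Period effects added |
|---|---|---|---|
| 0 | 5.8% | 5.7% | 5.8% |
| 2 | 11.7% | 10.8% | 6.0% |
| 5 | 36.9% | 38.2% | 4.5% |
| 10 | 91.3% | 94.7% | 4.9% |

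**Price of period effects.** The Hussey-Hughes variance with I = 8, T = 9, U = 36, W = V = 204, σ² = 0.1344 × 0.995/30 = 0.004458 and τ² = 0.1344 × 0.005 = 0.000672 is

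Iσ²(σ² + Tτ²)/[(IU − W)σ² + (U² + ITU − TW − IV)τ²] = 0.0003746/(84 × 0.004458 + 420 × 0.000672) = 0.0005705.

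The SE is 0.0239, against 0.0171 without periods. Power is Φ(0.12/0.0239 − 1.96) = 0.999. With exposure kept as well, power is 0.997 at week 0 and 0.994 at mean exposure.

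**The case against.** The strongest reply is that this is a condensed article. It says what the analyses will use, does not say that nothing else will be used, and writes out no model equation. An analysis plan that is not shown may contain period effects. That possibility is real. But the article does not leave the time structure open: it picks one time variable for each and all analyses, justifies it by bedding-in and accumulation, and gives the same terms twice. A model built to that text lacks calendar time.

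Several stronger readings are tempting and are not supported:

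- *All of the trend is credited to My Therapy.* The share is 37% to 50% of a linear trend.
- *The primary result is merely a before-after comparison.* Wards in both conditions run concurrently in most blocks, and a random-ward model uses some of that information.
- *The error rate is badly inflated whatever is tested.* An uncentred week-0 coefficient is much less affected. The article states neither the coding of exposure nor the primary contrast.
- *The Christmas bed closures show that outcomes drift.* They appear only as a sample-size allowance. Nothing says they change FIM gains, and they are not a linear trend.
- *The exposure term must be demoted to a secondary analysis.* That is a preference. The article gives a reason for the term, and it can stay if calendar time is in the model.

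**Conclusion.** The point stands as a fault in the model terms as written. With one ward crossing per step, condition and calendar time are about 20 weeks apart on average, and the exposure term cannot separate them. With no trend there is no bias. An upward trend is partly credited to My Therapy, and a downward one masks benefit.

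The error rates are illustrative. They rest on the assumed drift, its linearity, 30 patients per ward-block, ICC 0.005 and the outcome variance used. The direction and the share of trend absorbed follow from the layout and the ICC. The economic models share the structure, so the same mechanism applies to them, but its size in cost or QALYs was not calculated. The matter should be settled before analysis because it bears on the validity of the primary test.

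**What to change.** Add calendar time to every between-condition clinical and cost model, alongside the random ward effect and the My Therapy indicator. Fixed effects for the nine six-week periods are the direct choice; another prespecified function of calendar time would also serve. The secondary outcomes now compared univariably need the same term. Keep any weeks-of-exposure term only together with the period effects, and state how exposure is coded and which My Therapy contrast is the primary test.

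The cost is wording and some precision. The SE of the average effect rises by about 40% (0.0239/0.0171 = 1.40). The stated power of 0.99 still holds at 2,160, with or without the exposure term. No extra patients are needed, and no extra data either, because admission and discharge dates are already needed for length of stay.
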